### Participants

The trial will recruit 330 high surgical risk patients eligible for liver resection (165 in each arm). High-risk patients are defined as any patients that meet at least one of the following criteria: considered high-risk due to age (e.g. > 75 years); major co-morbidities as judged by the treating clinician; liver metastases with poor prognosis or high-risk surgery due to the tumour burden.

Patients will be identified for trial eligibility at the specialist liver multi-disciplinary treatment (sMDT) meeting. Suitability for inclusion into the trial will be assessed according to the following eligibility criteria.

#### Inclusion/exclusion criteria

Inclusion criteriaAge ≥ 18 yearsAble to provide written informed consentMDT diagnosis of colorectal liver metastases considered to be resectable or ablatable with curative intentResected colorectal primary or plan for primary resection with curative intentMeets *one or more* of the following criteria:Considered high-risk for surgery due to age (based on local policy)Major co-morbidities as judged by the treating clinician. Examples include history of myocardial infarction, severe chronic airway disease, major cerebrovascular accidents (CVA), pulmonary embolism (PE)Liver metastases with poor prognosis and high-risk surgery due to tumour burdenExamples include extensive synchronous disease, need for two stage resection or ALPPS, small anticipated remnant liver volume, curable extra-hepatic disease, downstaged with chemotherapy, poor response after chemotherapy but still resectable or ablatableSuitable candidate for either liver resection surgery or thermal ablation as judged by the MDTAble and willing to comply with the terms of the protocol including health-related quality of life (HRQoL) questionnaires

Exclusion criteriaIncurable extra-hepatic metastasesNot a suitable candidate for liver resection surgeryNot a suitable candidate for thermal ablationConcurrent malignant disease (except basal cell carcinoma)Patients who have undergone previous surgery or ablation for CLMPlanned simultaneous resection of primary and liver metastasesPregnancy

All patients will provide written informed consent. Patients will then be randomised on a 1:1 basis to receive either thermal ablation or surgical resection. A computer-generated minimisation programme that incorporates a random element will be used to ensure treatment groups are well-balanced for the following participant characteristics:Research siteSynchronous/metachronous diseasePrimary cancer in situ (Yes/No)High-risk for surgery due to age (Yes/No)Major co-morbidity (Yes/No)Poor prognosis or high-risk surgery due to tumour burden (Yes/No)Largest lesion size ≤ 5 cm (Yes/No) [13]Planned surgical resectionOpenLaparoscopicPlanned ablative treatmentRFAMWA

Blinding will not be performed.

### Pre-treatment investigations

Pre-treatment investigations and preparation will be as per institutional protocol but must include a baseline staging computed tomography (CT) scan of chest, abdomen and pelvis minimum and tumour markers (CEA as a minimum) within six weeks of the start of treatment.

### Definition of index disease

Index disease is defined as the disease distribution of CLM metastases at the time of the most recent sMDT review before the treatment commencing.

### Intervention: thermal ablation (RFA or MWA)

#### Definition of the intervention in the ablation arm

For patients in the ablation arm, the intervention is defined as the collection of ablation sessions conducted as treatment for the index disease (as defined above). Either RFA or MWA will be carried out according to the local availability of equipment and expertise. Ablation may also be performed at laparoscopic or open surgery if the percutaneous approach is contraindicated. Minimum standards for delivery of ablation to be achieved during the trial will be agreed by all centres in a pre-trial standardisation meeting.

#### End of the intervention in the ablation arm

End of trial treatment in the ablation arm is defined as the end of the final ablation session in the collection of ablation sessions conducted as treatment of the index disease.

### Control: surgery

#### Definition of the intervention in the surgical resection arm

For patients in the surgical arm, the intervention is defined as the collection of operations conducted as treatment for the index disease (as defined above). Liver resection will be carried out as per centre protocol. The majority of patients will have undergone resection of the primary cancer. Patients may be offered open or laparoscopic liver resection depending on site and stage of disease. In selected cases, the liver first approach may be considered. Procedures for patients with extensive metastatic disease will include two-stage liver resection, venous embolisation or the ALPPS procedure (Associated Liver Partition and Portal vein ligation for Staged hepatectomy). Minimum surgical outcomes to be achieved during the trial will be agreed by all centres in a pre-trial standardisation meeting.

#### End of the intervention in the surgical arm

End of trial treatment in the surgical resection arm is defined as the end of the final operation in the collection of operations conducted as treatment of the index disease.

### Post-treatment care

Participants will be reviewed in clinic at 3, 6, 12, 18 and 24 months post randomisation. Follow-up imaging investigations (CT scan chest, abdomen and pelvis minimum) and tumour markers will be performed following completion of successful treatment of the index disease until disease recurrence.

### Further treatments

Further chemotherapy will be offered to patients as per current practice. There is currently no evidence from RCTs that adjuvant chemotherapy after surgical resection of CLM improves overall survival [33]. However, adjuvant chemotherapy after surgical resection improves DFS [33] and may be used in many centres. Treatment of recurrent disease will depend on the site and extent of disease and will be decided following review at the sMDT review and following discussion of the treatment options with patients and their family. Surgery and ablation are potentially curative treatment options for recurrent CLM [34–36]. If surgery or ablation is not considered feasible, then palliative chemotherapy is usually administered. The median survival for non-resectable recurrent CLM is approximately 15 months [36].

### Participant-completed questionnaires

Participant-completed questionnaires measuring quality of life (EQ-5D, EORTC QLQ-C30, EORTC LMC21) will be completed in clinic at baseline (following consent but before randomisation) and at 3, 6, 12, 18 and 24 months post randomisation. Patient-completed questionnaires measuring health and social care resource use will be completed at 3, 6, 12, 18 and 24 months post randomisation.

### Longer-term follow-up

Five-year survival data will be obtained from the Office of National Statistics (ONS).

### CT scan central review

All CT scans performed to assess the outcome of the ablation intervention (e.g. baseline scans and scans typically carried out around 4–6 weeks after the last ablative session of treatment) will be centrally reviewed for participants in the thermal ablation arm during the pilot phase. The central review will facilitate quality assurance of local interpretation of the CT scan findings, e.g. the completeness/‘success’ of the treatment, the need for further sessions, etc. To ensure quality assurance following the pilot study, review of thermal ablation will be carried out by the trial interventional radiologists in a further 20% of the patients chosen at random.

To ensure quality assurance of the reporting of recurrence, which feeds into the primary endpoint, a subset of CT scans performed during the follow up period (e.g. baseline scans and scans at around 3, 6, 12, 18 and 24 months post randomisation) will be chosen at random for central review. The selection process will be stratified by centre and outcome (recurrence/no recurrence) so that the accuracy of reporting of both ‘recurrence’ and ‘no recurrence’ can be assessed across all participating centres.

### Trial organisation

The LAVA trial is funded by the NIHR HTA Programme (grant reference 13/153/04). The trial is sponsored by University College London (UCL). The Clinical Trials Research Unit (CTRU) at the University of Leeds are responsible for the coordination of the trial. Trial supervision will be established according to the principles of Good Clinical Practice (GCP) and in line with the NHS Research Governance Framework (RGF). This includes the establishment of a core Project Team, Trial Management Group (TMG), an independent Trial Steering Committee (TSC) and DMEC.

### Ethical considerations

The trial will be performed in accordance with the recommendations guiding physicians in biomedical research involving human subjects adopted by the 18th World Medical Assembly, Helsinki, Finland, 1964, amended at the 64th World Medical Association General Assembly, Fortaleza, Brazil, October 2013. Informed written consent will be obtained from the participants before randomisation into the trial. The right of a patient to refuse participation without giving reasons must be respected. The participant must remain free to withdraw at any time from the trial without giving reasons and without prejudicing his/her further treatment. The trial has obtained ethical approval in the UK and in the Netherlands.

### Endpoints

#### Primary endpoint

DFS at two years post randomisation.

DFS is defined as the time from randomisation to the first event, which is defined as any of the following:Local, regional or extra hepatic/systemic recurrence of diseaseDeath (any cause)

The time-to-event for patients whose treatment fails will be set equal to 0. If, according to post-intervention assessment, the index disease is deemed to have not been successfully removed/eradicated, then the treatment will be classed as having ‘failed’. Local recurrence is defined as the detection of disease at the treatment site after successful trial intervention. Regional recurrence is defined as detection of disease in the liver—not related to the treatment site—after successful trial intervention.

Extra-hepatic/systemic recurrence is defined as detection of new disease at any site other than the liver after successful trial intervention. ‘New disease’ refers to any extra-hepatic/systemic disease which was not already detected before commencement of trial treatment. The date of recurrence is defined as the date of the relevant assessment which detected the recurrence.

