### Data analysis

#### Statistical analysis

Analysis and reporting will be in line with CONSORT guidelines. Analyses will be carried out on both an intention-to-treat (ITT) basis and per-protocol (PP) basis. Non-inferiority hypotheses will be tested at the one-sided 2.5% level of significance. Superiority hypotheses will be tested at the two-sided 5% level of significance. 95% confidence intervals for parameter estimates will also be reported.

The primary analysis will assess the difference in DFS. The non-inferiority hypothesis will be tested using an appropriate survival model to incorporate random effects with respect to research site and including adjustment for the stratification factors. The specific survival model that is most ‘appropriate’ cannot be determined a priori; for example, the Cox proportional hazards model will be considered but will not be used if the proportional hazards assumption is violated. Patients for whom an event is not reported during their trial follow-up will be censored at the last date that they were known to not have had an event.

Differences in rates such as complication rates and recurrence rates will be analysed using multi-level logistic regression incorporating random effects with respect to research site and will include adjustment for the stratification factors.

Subgroup analysis based on the type of surgery (open or laparoscopic liver resection) and type of ablation (RFA or MWA) will be performed. If there are truly substantial differences in efficacy between types of treatment within an arm, then these subgroup analyses, while likely having limited precision, will give an unbiased indication of the magnitude and direction of the differences. This will allow us to explore how the treatment effect partitions into these more precise components, which will allow us to assess the validity of assumption that there is no substantial difference in efficacy between open and laparoscopic surgery, and there is no substantial difference between RFA and MWA. This will also allow us to perform sensitivity analyses using imputation methods to assess the impact of changing the proportion of each type of treatment performed within arm on the primary treatment effect estimate. This will facilitate the generalisability of our inferences to wider practice and to potential changes in the uptake of each type of treatment over time.

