#### Method

##### Design: semi-structured interviews

A purposive sample of up to 20 patients will be recruited over nine months from across the pilot study sites, to include the three outcomes of consent: (1) participant consented and accepted treatment allocation; (2) participant consented to randomisation but refused the allocated treatment; (3) participant refused participation in the trial. In-depth, semi-structured interviews will explore patient perspectives of treatment, their understanding of the two treatments, reasons for taking part or refusing the trial and the acceptability of randomisation between the procedures.

A purposive sample of approximately 15 healthcare professionals (local principal investigators, recruiters) from across the pilot study sites will be interviewed. Participants will be selected on the basis of their ability to shed light on the recruitment process (initial discussion, recruiter interview). Interviews will explore their views about the trial, clinical equipoise and their understanding of the recruitment challenges.

Patient and staff interviews will be informed by a topic guide developed in conjunction with PPI representatives and informed by the literature. All interviews will be audio-recorded with permission.

Participant information sessions (recruiter encounters) will be audio-recorded (with permission) to examine how information is presented by recruiters and received and understood by patients, to identify issues potentially affecting trial recruitment. Information gleaned from the interviews and listening to the participant information sessions will inform the development of training materials for the main trial.

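### A randomised patient who never receives a trial procedure can have no DFS event except death, because recurrence and failure are both defined only after an intervention

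*Protocol article*

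**What the plan says.** All references are to the protocol article.

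- **Clock and events (Primary endpoint).** "DFS is defined as the time from randomisation to the first event, which is defined as any of the following": recurrence (local, regional or extra-hepatic) or death.
- **Recurrence (same section).** "Local recurrence is defined as the detection of disease at the treatment site after successful trial intervention". Likewise, "Regional recurrence is defined as detection of disease in the liver—not related to the treatment site—after successful trial intervention". Extra-hepatic recurrence has the same condition and must also be new, meaning "any extra-hepatic/systemic disease which was not already detected before commencement of trial treatment".
- **Failure (same section).** Time to event is set to 0, and the trigger is: "If, according to post-intervention assessment, the index disease is deemed to have not been successfully removed/eradicated".
- **Index disease (Definition of index disease).** It is fixed at the last specialist MDT review before treatment starts.
- **Intervention.** It is defined separately by arm: ablation sessions in one, operations in the other.
- **Analysis (Statistical analysis).** "Analyses will be carried out on both an intention-to-treat (ITT) basis and per-protocol (PP) basis". A patient without a reported event is censored when last known to be event-free.
- **Follow-up (Post-treatment care).** Clinic reviews run at 3, 6, 12, 18 and 24 months from randomisation. Imaging and tumour markers "will be performed following completion of successful treatment of the index disease until disease recurrence".
- **Non-uptake (Design: semi-structured interviews).** One interview group is: "participant consented to randomisation but refused the allocated treatment".

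**The concern.** The clock starts at randomisation, but every route to an event other than death opens only once a trial procedure has been given. An intention-to-treat analysis keeps patients who never reach that point. They are scored as event-free until death or censoring, although their metastases were never removed.

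Such patients are foreseeable. Eligibility rests on age, co-morbidity or tumour burden. The primary may still be in place. Surgery may be staged. Staging CT is required within six weeks of the start of treatment, so progression can come to light between randomisation and treatment. The trial is open and compares very different procedures, so nothing supports assuming equal non-treatment in the two arms. If the rates differ, the scoring rule itself can move the primary hazard ratio and the non-inferiority conclusion.

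**Working it through.** **1. Scoring by patient path, as printed**

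| Path after randomisation | DFS as printed |
|---|---|
| Procedure cancelled because progression is found | No event until death; otherwise censored |
| Never treated (unfit, or refuses all procedures) | No event until death; otherwise censored |
| Same disease found at operation and left behind | Failure, time 0 |
| Staged procedure started but not finished | Can be caught by the failure rule |
| Progresses, then treated | Earlier progression not counted; later failure or recurrence is |
| Given the other arm's procedure | Ambiguous: the intervention is defined by arm, but the endpoint says only *trial intervention* |

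Rows 1 and 3 may describe the same disease state, scored in opposite ways.

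**2. The plan's own figure**

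Inputs from Sample size calculations: DFS 14 months (read as a median), margin 4 months, one-sided 2.5%, 80% power, 48 months' accrual, 24 months' follow-up, 5% drop-out.

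- Margin: HR = 14/10 = 1.4.
- Events (Schoenfeld): 4 × (1.960 + 0.842)² / (ln 1.4)² = 278 after rounding up.
- P(event), with λ = ln 2/14 and follow-up to the end of the study: 1 − (e^(−24λ) − e^(−72λ))/(48λ) = 0.884.
- N: 278/0.884 gives 315, and 315/0.95 = 332, against 330 stated.

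The figure reproduces. The point does not depend on it, but it supports the set-up in step 4.

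**3. What death-only scoring does to one patient**

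P(event by 24 months) = 1 − 2^(−24/median).

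- Design DFS, median 14 months: 0.70.
- Death only, median 15 months (the article's figure for non-resectable *recurrent* disease, a different population): 0.67.
- Death only, median 30 months (assumption: 25% alive at five years, exponential, taken from the article's figure of over 25% after resection): 0.43.

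**4. Illustration at trial level**

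The documents give no non-treatment rate, so all rates below are assumed. There are 165 patients per arm and 1,500 simulated trials per row. Treated patients have exponential DFS with a resection median of 14 months. Follow-up is 24 to 72 months. An unadjusted Cox model is used, and non-inferiority (NI) is declared if the upper 95% limit is below 1.4. *As printed*: untreated patients have an event only at death (median 30 months). *Counted*: their progression is an event at 1 to 6 months.

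| HR in treated | Untreated, resection / ablation | As printed: HR, P(NI) | Counted: HR, P(NI) |
|---|---|---|---|
| 1.0 | 0 / 0 | 1.00, 81% | 1.00, 81% |
| 1.0 | 10% / 10% | 1.00, 80% | 1.00, 83% |
| 1.0 | 2% / 10% | 0.94, 92% | 1.08, 57% |
| 1.0 | 10% / 2% | 1.06, 64% | 0.93, 94% |
| 1.4 | 0 / 0 | 1.40, 2.5% | 1.40, 2.8% |
| 1.4 | 10% / 10% | 1.32, 5.7% | 1.36, 4.3% |
| 1.4 | 2% / 10% | 1.24, 17.9% | 1.48, 0.7% |
| 1.4 | 10% / 2% | 1.47, 0.9% | 1.28, 12.5% |

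**5. Sensitivity to the set-up**

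Follow-up fixed at 24 months, untreated median survival 15 to 30 months, counted events at 0.5 to 3.5 months, 3,000 trials per scenario:

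- Treated HR 1.0, untreated 3% / 10%: HR 0.95–1.00 and P(NI) 74–82% as printed; 1.10 and 46% counted.
- Treated HR 1.0, 10% / 3%: 1.00–1.05 and 58–70%; 0.91 and 90%.
- Treated HR 1.4, 5% / 15%: P(NI) 6.5–16% as printed; 0.3% counted.
- Treated HR 1.4, 15% / 5%: 0.7–2.6% as printed; 25% counted.

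Both set-ups agree. The gap between the rules is material when non-treatment is unequal, its sign follows the arm with more untreated patients, and it is small when the rates are equal.

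**The case against.** **Condensation.** Scoring of untreated and switched patients often sits in the full protocol or the analysis plan, neither of which is shown. That would excuse silence. Here, though, the article prints a definition, and the definition itself excludes these patients.

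**Counting progression is not neutral either.** With more untreated patients in the resection arm and a treated-patient HR of 1.4, the counted rule declares non-inferiority far more often (25% against 0.7–2.6%). This stands. The two rules answer different questions about whether non-delivery of treatment is a DFS failure, and the treated-patient HR is only a yardstick, not the intention-to-treat effect. A reader might infer that the printed rule favours ablation; the documents do not support any direction.

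**Existing safeguards.** A per-protocol analysis would normally leave out never-treated patients, so a discrepancy might show, and overall survival is unaffected. These help detection but do not repair the primary intention-to-treat result.

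**Stronger readings that fail.**
- That anyone who progresses before treatment can have no event but death: if then treated, the patient can still fail or recur.
- That switchers can have no event: *trial intervention* may cover either procedure.
- That the interview group of refusers shows how many go untreated: it is a sampling category without a rate, and a patient who refuses one arm may receive the other procedure.
- That these patients' events would go unrecorded: clinic reviews are timed from randomisation whatever the treatment, and CT scan central review describes scans at the same times. Only the imaging sentence is tied to successful treatment.

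**Conclusion.** The point holds for patients who never receive a trial procedure. As printed, they can have no DFS event but death and are otherwise censored with disease in place, while the same disease left behind at operation is an event at time 0. For switchers the text is ambiguous. For patients who progress and are then treated, only the earlier progression is lost.

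The effect on the primary result is a risk of unknown size and direction. With assumed non-treatment of 2% against 10% and equal DFS when treated, the choice of scoring moves the hazard ratio by 0.13 to 0.14 (0.94 to 1.08, or 1.06 to 0.93) and the chance of declaring non-inferiority by 30 to 35 percentage points. This rests on the assumed rates, a 30-month median survival in untreated patients and exponential times. With 15-month survival the printed rule scores untreated patients much like treated ones. With equal rates the choice hardly matters. It should be settled before analysis because it governs the primary comparison.

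**What to change.** Amend Primary endpoint, in the same words for both arms:

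1. For a patient who does not receive a trial procedure, progression or new disease inside or outside the liver detected after randomisation is a DFS event, dated at detection.
2. Recurrence after whichever curative procedure was actually given is a DFS event.
3. State one prespecified, arm-neutral rule for patients whose index disease is never treated, with a sensitivity analysis under the alternative scoring. A refusal or a clinician's decision should not become an event automatically: in an open trial that is a separate and debatable choice of estimand.

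Amend Post-treatment care so that disease status at 3, 6, 12, 18 and 24 months and available scan results are collected for every randomised patient until a DFS event, whether or not treatment was completed.

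Cost: endpoint and follow-up wording, one case report form item (procedure not given, with date and reason), and DFS that looks slightly less favourable.

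### DFS is timed from randomisation, but a patient who is never treated can have no DFS event except death, and new extra-hepatic disease found before treatment is never counted

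*Protocol article*

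**What the plan says.** All references are to the protocol article.

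- **Time origin** (Primary endpoint): "DFS is defined as the time from randomisation to the first event". The events are recurrence (local, regional or extra-hepatic) and death from any cause.
- **Local recurrence** (Primary endpoint): "Local recurrence is defined as the detection of disease at the treatment site after successful trial intervention".
- **Regional recurrence** (Primary endpoint): "Regional recurrence is defined as detection of disease in the liver—not related to the treatment site—after successful trial intervention".
- **Extra-hepatic recurrence** (Primary endpoint): this carries the same condition of a successful intervention, and the disease must also be new. New disease "refers to any extra-hepatic/systemic disease which was not already detected before commencement of trial treatment", so the cut-off is the start of treatment and not randomisation.
- **Treatment failure** (Primary endpoint): the event time is set to 0 when an assessment made after the intervention finds that the index disease was not cleared.
- **Index disease** (its own section under Methods): "Index disease is defined as the disease distribution of CLM metastases at the time of the most recent sMDT review before the treatment commencing".
- **Analysis sets** (Statistical analysis): "Analyses will be carried out on both an intention-to-treat (ITT) basis and per-protocol (PP) basis". Patients without a reported event are censored when last known to be event-free.
- **Untreated patients are foreseen** (Qualitative sub-study, Method): one planned interview group is patients who consent to randomisation and then refuse the allocated treatment.

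**The concern.** The clock starts at randomisation, but only death can stop it until an intervention has been given. Between those two points the endpoint does not measure time free of disease.

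The scoring also ranks patients in the wrong order. A patient who is treated but not cleared gets the worst possible value, 0. A patient whose disease advances until treatment is abandoned gets time to death. In an open trial, the decision whether to attempt treatment can move the same patient from one score to the other.

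The share of such patients need not be equal by arm. The resection pathway may involve staged operations or venous embolisation, and ablation may need several sessions. If the shares differ, the comparison of arms on the primary endpoint is distorted.

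**Working it through.** **1. The planned sample size, for orientation.** The inputs are in Sample size calculations: margin 4 months on a DFS of 14 months (read as a median), 80% power, one-sided 2.5%, four-year accrual, two-year follow-up, 5% drop-out. With exponential times the margin is HR 14/10 = 1.40. Events = 4 × (1.960 + 0.842)² / (ln 1.40)² = 278. With uniform accrual and follow-up of 24 to 72 months, the event probability is 0.884. So N = 278/0.884 = 315, and 315/0.95 = 332, against 330 stated. The figure reproduces, and this point does not depend on it.

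**2. What each kind of patient scores as worded.**

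- Treated, index disease not cleared: failure, time 0.
- Treated and cleared: time to later recurrence or death.
- New liver lesion while waiting, still treated: the lesion becomes index disease. If it is not cleared the score is 0; if it is cleared, later recurrence counts. Only the progression found while waiting is lost.
- New extra-hepatic disease while waiting, still treated: that disease is never an event; later new disease, failure or death still counts.
- Never treated (refusal, or progression beyond treatment): neither recurrence nor failure can be met. The event is death, otherwise the patient is censored.

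**3. Effect on the DFS curve.** The article gives no survival figure for never-treated trial patients. The nearest is in Further treatments: "The median survival for non-resectable recurrent CLM is approximately 15 months". I use it only as a proxy; it describes a different population. Treated patients have a DFS median of 14 months, and the never-treated share is assumed to be 10%.

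- 12 months, treated: 0.5^(12/14) = 0.552. Never treated: 0.5^(12/15) = 0.574. As worded: 0.9 × 0.552 + 0.1 × 0.574 = 0.554. Counted as events at 0: 0.9 × 0.552 = 0.497.
- 24 months, by the same formula: 0.307 as worded, 0.274 counted.
- With a 5% share the 12-month values are 0.553 and 0.524; with 15% they are 0.555 and 0.469.

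On this proxy, not being treated does not register as a poor outcome: 15 months against the 14 assumed for the resection arm.

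**4. Effect on the HR (ablation vs resection).** Simulation with exponential times, a 24-month cap and a Cox model. Never-treated patients either die with median 15 months (as worded) or have an event at 1.5 months (counted). All shares are assumptions, because the documents give none. I reran it with 1,000,000 patients per arm.

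Treated patients doing equally well in both arms (true HR 1.00):

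| Never treated, resection / ablation | HR as worded | HR if counted |
|---|---|---|
| 5% / 5% | 1.00 | 1.00 |
| 10% / 10% | 1.00 | 1.00 |
| 3% / 5% | 1.00 | 1.03 |
| 3% / 10% | 1.00 | 1.10 |
| 10% / 3% | 1.00 | 0.91 |

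Treated patients at the margin (true HR 1.40):

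| Never treated, resection / ablation | HR as worded | HR if counted |
|---|---|---|
| 10% / 10% | 1.35 | 1.35 |
| 3% / 10% | 1.35 | 1.49 |
| 10% / 3% | 1.39 | 1.25 |

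Against the margin on the log scale, ln(1.10)/ln(1.40) = 0.095/0.336 = 0.28, and ln(0.91) gives the same size with the opposite sign.

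**The case against.** The strongest counter-arguments are these.

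- **Most patients who progress while waiting may still be treated.** A reader might infer that everyone who progresses on the waiting list counts as disease-free until death. The text does not support that. Index disease is set at the last review before treatment, so these patients can fail at time 0 or recur later. Never-treated patients can also be censored. This stands and limits the point to never-treated patients and to disease found before treatment.
- **The direction is unknown.** A reader might infer that the wording favours a non-inferiority claim because it pulls the HR towards 1. With equal shares, both scorings give about the same HR. With more such patients in the resection arm, the wording works against ablation. The article does not say which arm would have more. This stands.
- **The size rests on assumed shares and a borrowed survival figure.** This stands. With 3% against 5%, the HR moves by only about 3%.
- **Other analyses cover the gap.** Only in part. Overall survival is a separate outcome, DFS from the end of intervention has no start date for an untreated patient, and a per-protocol analysis does not repair the ITT one.
- **The full protocol or analysis plan may hold a rule.** It may, but it would have to override an endpoint definition that the article prints in full. This is a stated rule that scores badly, not an omitted detail.
- **Freezing index disease at randomisation would bring its own problem.** The baseline CT is tied to the start of treatment (Pre-treatment investigations) and may come after randomisation, so lesions already present could be scored as progression. This stands, and the fix below leaves that definition alone.

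**Conclusion.** The point holds in a limited form. As printed, the primary ITT endpoint has no event other than death for a randomised patient who is never treated, and it ignores new extra-hepatic disease found between randomisation and treatment. A treated but uncleared patient meanwhile scores 0.

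Relative to counting such patients, DFS is overstated in both arms: by about 0.06 at 12 months if 10% are never treated and they are scored at time 0. The HR is affected materially only if the shares differ by arm. Assumed shares of 3% and 10% shift it by about 10% in either direction, or 0.28 of the log margin. These sizes rest on exponential times, the assumed shares and the 15-month proxy. The documents do not support a claim of bias in favour of ablation.

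**What to change.** For the primary ITT endpoint, add two events to the definition:

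- (a) new extra-hepatic disease detected after randomisation and before treatment starts, dated at detection;
- (b) index disease that is never treated, dated when the decision not to treat, or the progression, is established.

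Add a sensitivity analysis that scores (b) at time 0, to match the existing failure rule. Leave the index-disease definition unchanged, and keep the conditions on successful intervention for the secondary recurrence outcomes.

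The cost is endpoint wording and one extra CRF date. There will be slightly more early events in both arms. Detection under (a) will depend on when patients are scanned before treatment, because scheduled follow-up imaging begins only after successful treatment (Post-treatment care). Reporting by arm the number of patients under (a) and (b), and the time from randomisation to treatment, would show whether the imbalance examined here arises.
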